### Sample size

2.19

An a priori sample size calculation was conducted using G*Power version 3.1.9.7 [56, 57]. Using an allocation ratio of 1:1, power of 80%, assuming a minimal clinically important difference of 1.1 points [20] (representing a medium effect size [Cohen's *d*] of 0.5), standard deviation of 2.2 points [20], alpha set at 0.05 and allowing a 10% participant loss to follow‐up [20], a sample size of at least 140 participants (i.e. approximately 70 per group) will be required.

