### Statistical analysis

2.20

Statistical analysis will be performed using the most recent version of SPSS available to the researchers using the intention‐to‐treat principle for all randomised participants. In participants with bilateral symptoms, the more painful side will be analysed (or the right lower limb if they cannot decide which is the more painful side) to maintain independence of data [58]. Standard tests to assess continuous data for normal distribution will be used. If continuous data is not normally distributed, transformation will be carried out if appropriate. Multiple imputation will be used to replace any missing data using five iterations, with sex, age, baseline scores and group allocation as predictors [59]. The exception will be for the GROC scale, co‐interventions, adherence and adverse events where no data substitution will be applied.

The primary outcome measure will be NRS pain measured at 12 weeks. To avoid over‐testing and to minimise the risk of type I error associated with serial measurements, statistical analysis of the efficacy of the interventions will specifically focus on the between group difference at 12 weeks [60, 61]. Differences in the primary and secondary outcome measures between the two groups will be compared. Continuously scaled outcome measures will be analysed using the analysis of covariance (ANCOVA) with baseline scores and intervention group entered as independent variables [62, 63]. Dichotomous outcome measures (e.g. frequency of adverse events, frequency of co‐interventions and dichotomised GROC) will be compared using relative risk, risk difference and number needed to treat. Intervention adherence will be compared using independent group *t*‐tests. For all analyses, both 95% confidence intervals and *p*‐values will be generated where appropriate.

A sensitivity analysis will be conducted to estimate treatment effects on the primary outcome. We will assess the robustness of the results from our analyses using the following conditions: (i) complete case analysis—only analyse participants who provide outcome data and (ii) last observation carried forward. A sensitivity analysis will also be undertaken to estimate treatment effects on the primary outcome assuming full adherence (per‐protocol analysis) [64]. Full adherence will be defined as participants reporting wearing the shoe inserts for an average of at least 35 h per week.

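### The primary imputation is set at five iterations with no stated number of imputed data sets; if five data sets are meant, a week-12 result near p = 0.05 is not reproducible

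*Protocol article*

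**What the plan says.** The Statistical analysis section of the protocol article states "Multiple imputation will be used to replace any missing data using five iterations", "with sex, age, baseline scores and group allocation as predictors". It gives no other number of imputations and no seed. The software is SPSS.

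This setting governs the primary analysis. The section says "The primary outcome measure will be NRS pain measured at 12 weeks". Pain is not among the outcomes exempted from imputation, a list that ends with "adherence and adverse events where no data substitution will be applied". The analysis model is ANCOVA "with baseline scores and intervention group entered as independent variables". The complete-case and last-observation analyses ("only analyse participants who provide outcome data and (ii) last observation carried forward") are sensitivity analyses only.

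The Sample size section sets the expected amount of missing data, "allowing a 10% participant loss to follow"-up, which is about 14 of 140 participants.

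**The concern.** In chained imputation, iterations are the cycles run before one completed data set is drawn. The Monte Carlo error of the pooled estimate and p-value depends on a different setting, the number of completed data sets. The sentence can be read in two ways.

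- **Five cycles.** The number of data sets is then unstated. The setting that is fixed matters little here, because the listed predictors are baseline variables and the Randomisation section has all baseline assessments done before allocation.
- **Five data sets.** This is the likelier intent. The random seed then contributes visible noise to the pooled result.

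The efficacy conclusion rests on one comparison at 12 weeks. If that result falls near 0.05, re-running the same plan on the same data with another seed could change the stated conclusion.

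**Working it through.** **Inputs from the protocol article.** N = 140 allocated 1:1, SD 2.2, difference 1.1, alpha 0.05, power 80%, 10% loss (Sample size); imputation predictors sex, age, baseline score and group, and ANCOVA on baseline and group (Statistical analysis).

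**Assumptions not in the documents.** Baseline to week-12 correlation 0.5; outcomes missing completely at random; missing fraction varied from 5% to 20% around the stated 10%; normally distributed scores.

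**Step 1: the plan's own figure.** n per arm = 2 × (1.96 + 0.842)² × 2.2² / 1.1² = 62.8, rounded up to 63. Then 63 / 0.9 = 70 per arm, 140 in total. The stated sample size reproduces and is not affected by this point.

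**Step 2: efficiency with five data sets.** Relative efficiency = 1 / (1 + fraction of missing information / m). With a fraction of 0.10 and m = 5, this is 1 / (1 + 0.02) = 0.98.

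**Step 3: Monte Carlo error of the estimate.** The week-12 score was imputed by Bayesian normal regression on the planned predictors and pooled by Rubin's rules with Barnard-Rubin degrees of freedom. The imputation was redrawn 300 times on each of 40 simulated data sets. At 10% missing:

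- m = 5: seed-to-seed SD 0.051 points against a standard error of 0.356, a ratio of 0.14.
- m = 50: 0.016 against 0.343, a ratio of 0.045.

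Theory gives the ratio as √(λ / (m + 1)), where λ is the between-imputation share of the total variance. With the simulated λ this is √(0.116 / 6) = 0.139 and √(0.104 / 51) = 0.045, in agreement.

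**Step 4: the p-value near the threshold.** Each data set was shifted so that its complete-case p was exactly 0.05. The 95% range of the pooled p across seeds was:

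| Missing | m = 5 | m = 20 | m = 50 | m = 100 |
|---|---|---|---|---|
| 5% | 0.032–0.084 | 0.040–0.065 | 0.045–0.060 | 0.046–0.057 |
| 10% | 0.026–0.110 | 0.036–0.073 | 0.041–0.064 | 0.044–0.061 |
| 20% | 0.017–0.158 | 0.031–0.090 | 0.037–0.074 | 0.040–0.065 |

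**Step 5: how often two seeds disagree on p < 0.05, over all trials** (600 simulated trials per setting):

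| True difference | 10% missing, m = 5 | 10%, m = 50 | 20% missing, m = 5 | 20%, m = 50 |
|---|---|---|---|---|
| 0 | 2.2% | 0.6% | 3.4% | 1.0% |
| 0.6 | 7.2% | 1.8% | 10.7% | 4.0% |
| 1.1 | 4.5% | 1.1% | 8.4% | 1.9% |

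A separate simulation with a true difference of 0.75 kept only trials whose median p lay between 0.02 and 0.10. There, at 10% missing, two seeds disagreed in 25% with m = 5 and 9% with m = 50. Those rates apply to near-threshold trials only.

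**Step 6: validity at 10% missing.** Rejection rates were 0.044 (m = 5) and 0.048 (m = 50) under no difference, and 0.885 and 0.883 at a difference of 1.1. At 0.6 they were 0.386 and 0.423. The two values of m used different simulated trials, so that gap of 0.037 has a simulation standard error of √(0.386 × 0.614 / 600 + 0.423 × 0.577 / 600) = 0.028 and is compatible with chance.

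**Step 7: the assumed correlation.** Baseline is in both the imputation model and the ANCOVA, so in this linear setting the correlation only rescales the residual SD. The p-value ranges in step 4 do not depend on it. The SD of 0.051 points scales with √(1 − r²): 0.051 × 0.954 / 0.866 = 0.056 at r = 0.3, and 0.051 × 0.714 / 0.866 = 0.042 at r = 0.7. For the non-zero differences in step 5, another correlation acts like a somewhat different true difference.

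**The case against.** The strongest reply is that nothing inferential is broken. At five data sets and 10% loss, efficiency is about 98%, the error rates are essentially those obtained with 50, and the Monte Carlo SD of about 0.05 points is under 5% of the 1.1-point target difference. The planned complete-case analysis is also a seed-free check. With only the outcome missing, and an imputation model that adds just age and sex to the ANCOVA covariates, it estimates nearly the same thing, so a verdict flipped by an unlucky seed would show against it. Confidence intervals are planned as well, and any finite number of data sets leaves some dependence on the seed. All of this stands, and it is why the point is minor.

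It does not remove the point. The complete-case result is a sensitivity analysis and does not decide the primary conclusion. The plan states a number, and another number is clearly better at almost no cost.

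A reader might also infer that the authors have confused cycles with data sets. The documents do not show this: the word may be loose usage for five imputations, or it may mean five cycles with the number of data sets given in a document not shown. On that second reading, too few data sets does not follow at all.

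**Conclusion.** The wording should be corrected, and on the likelier reading the setting should be raised. With five imputed data sets and 10% missing, the seed alone moves the estimate with an SD of about 0.05 points (14% of its standard error). Around a complete-case p of 0.05 it moves the pooled p over about 0.026 to 0.110. Fifty data sets narrow this to 0.041 to 0.064 and cut disagreement between seeds about three- to fourfold.

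A stronger reading, that the primary analysis is invalid or that its p-value is generally arbitrary, is not supported. Error rates hold, and the conclusion is exposed only when the result lies near the threshold. The 25% disagreement rate must not be read as a rate for all trials. Nor is there computed support for a fixed minimum number of chain cycles.

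The figures rest on reading five as the number of data sets, on data missing completely at random, and on an assumed correlation of 0.5, which affects the points scale but not the p-value ranges. Severity: minor.

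**What to change.** In the Statistical analysis section, replace the reference to five iterations with wording such as: *at least 50 imputed data sets will be generated, using a random seed recorded before unblinding, and results will be pooled by Rubin's rules; the Monte Carlo error of the primary treatment estimate will be reported.* No minimum number of cycles is needed.

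The cost is one sentence and a few minutes of computing. Sample size, data collection and participants are unaffected. Some dependence on the seed remains; recording the seed makes the run repeatable, and the reported Monte Carlo error shows how much noise is left.

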### Baseline assessments

2.5

Participant characteristics (such as age, gender, sex, country of birth, ethnicity, education, major medical conditions, medications and foot pain duration) will be obtained upon enrolment via an online questionnaire designed in a secure web platform (REDCap™, Research Electronic Data Capture, Vanderbilt University, USA). The following anthropometric measurements and clinical assessments will be conducted in person: (i) height and weight will be measured using a digital scale and body mass index will be calculated as weight (kg)/height (m^2^), (ii) foot pain and location will be determined by clinical assessments, such as palpation and passive range of motion testing [28], and self‐reported using a standardised foot manikin diagram (^©^The University of Manchester 2000. All rights reserved) [26], (iii) static foot posture will be assessed using the Foot Posture Index [29], (iv) foot and ankle range of motion will be measured based on previously published, reliable protocols [30, 31], (v) foot and ankle muscle strength will be measured with a CITEC hand‐held dynamometer (CIT Technics, The Netherlands) using a previously documented, reliable protocol [32], and (vi) footwear will be assessed using selected items from the Footwear Assessment Tool [33].

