### Outcome measures

2.12

The primary outcome will be measured prior to allocation at baseline and at 12 weeks (the primary endpoint). All secondary outcomes unless stated otherwise will be measured prior to allocation at baseline and at 4, 8 and 12 weeks. Participants will complete online questionnaires at 4 week intervals, and they will be encouraged to contact the researchers at any time during the trial if needed. The outcome measures and associated timepoints are shown in Table 1.

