#### Participants' perception of overall treatment effect

2.14.2

Participants' perception of overall treatment effect will be measured using the self‐reported global rating of change (GROC) scale [47] at 12 weeks. Participants will be asked: ‘With respect to your midfoot osteoarthritis, how would you describe yourself now compared to the start of the study?’, with the response measured using a 15‐point Likert scale (ranging from ‘a very great deal worse’ to ‘a very great deal better’). This outcome will then be dichotomised into the categories of ‘effective’ (‘a very great deal better’, ‘a great deal better’, ‘a good deal better’ and ‘moderately better’) and ‘ineffective’ (‘somewhat better’, ‘a little better’, ‘about the same, hardly any better at all’, ‘no change’, ‘about the same, hardly any worse at all’, ‘a little worse’, ‘somewhat worse’, ‘moderately worse’, ‘a good deal worse’, ‘a great deal worse’ and ‘a very great deal worse’) [48].

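### No covariate is named for the dichotomised global rating of change, although baseline pain is collected: the comparison is valid, but a small gain in precision is left unused

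*Protocol article*

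**What the plan says.** The Statistical analysis section sets one method for each type of outcome. Continuous outcomes get "analysis of covariance (ANCOVA) with baseline scores and intervention group entered as independent variables". Dichotomous outcomes, with adverse events, co-interventions and dichotomised GROC given as examples, "will be compared using relative risk, risk difference and number needed to treat". No covariate appears in that sentence. The section also calls for 95% confidence intervals and p-values, and it rules out imputation for GROC, co-interventions and adverse events.

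The section on outcome measures states that "The primary outcome will be measured prior to allocation at baseline and at 12 weeks (the primary endpoint"), so baseline NRS pain exists for everyone randomised. The rating itself, the "self‐reported global rating of change (GROC) scale", is collected at 12 weeks only and has no baseline score of its own. The Randomisation section describes 1:1 allocation in permuted blocks of 4 and 6 and names no stratification factor.

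**The concern.** The plan treats its two kinds of outcome differently. Where it intends a covariate it names one, and for GROC it names none. The natural reading is therefore a two-by-two comparison.

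A participant who starts with more pain has more room to improve, so baseline pain should carry some information about a rating of change. The design does not balance baseline pain between arms beyond what simple chance gives. Adjustment removes that chance component from pain and function but not from GROC, so the two could drift apart for a reason unrelated to treatment. GROC is a named secondary efficacy outcome, and its number needed to treat is a figure that readers are likely to quote.

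**Working it through.** **Numbers analysed.** With a difference of 1.1, SD of 2.2, 80% power and two-sided alpha of 0.05 (Sample size section; two-sided is assumed): n per arm = 2 × (1.96 + 0.8416)² × (2.2/1.1)² = 62.8, so 63. Then 63/0.9 = 70 per arm, or 140 in total, as the protocol states. GROC is not imputed, so about 63 per arm would be analysed.

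**Inputs not in the protocol (assumed).** GROC success 40% versus 60%; follow-up pain SD 2.2; baseline pain SD s_B of 2.2 or 1.5, the lower value because entry requires pain of at least 3 out of 10; baseline to week-12 pain correlation r of 0.3 to 0.7; correlation g between GROC and pain improvement of 0.6 to 0.8. Baseline pain is assumed to act on GROC only through improvement.

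**Step 1: baseline pain against improvement.** c = (s_B − r·s_F) / √(s_B² + s_F² − 2·r·s_B·s_F).
- Equal SDs: c = √((1 − r)/2), which is 0.59 at r = 0.3, 0.50 at r = 0.5 and 0.39 at r = 0.7.
- s_B = 1.5, s_F = 2.2, r = 0.5: c = (1.5 − 1.1)/√(2.25 + 4.84 − 3.30) = 0.4/1.947 = 0.21.

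**Step 2: baseline pain against the dichotomised rating.** Cutting a normal variable at 40% multiplies a correlation by 0.386/√(0.4 × 0.6) = 0.79. So ρ = 0.79 × g × c.

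**Step 3: variance saved.** Adjustment removes about ρ² of the variance of the risk difference.

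| Baseline SD | r | g | c | ρ | ρ² |
|---|---|---|---|---|---|
| 2.2 | 0.3 | 0.8 | 0.59 | 0.37 | 14% |
| 2.2 | 0.5 | 0.8 | 0.50 | 0.32 | 10% |
| 2.2 | 0.5 | 0.6 | 0.50 | 0.24 | 6% |
| 2.2 | 0.7 | 0.6 | 0.39 | 0.18 | 3% |
| 1.5 | 0.5 | 0.8 | 0.21 | 0.13 | 2% |
| 1.5 | 0.5 | 0.6 | 0.21 | 0.10 | 1% |

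Simulation with 63 per arm, comparing the crude risk difference with the one standardised from a logistic model, agrees. The reduction is about 5% to 13% with equal SDs and r of 0.3 to 0.5, about 2% to 7% with equal SDs and r = 0.7, and about 0% to 6% with a narrowed baseline SD. At the top end the interval shrinks by 1 − √(1 − 0.13) = 7%.

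**Step 4: bias.** In simulations over a range of covariate strengths, the crude risk difference missed the true value by at most 0.0025 on average. Crude and adjusted estimates centred on the same value.

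**Step 5: chance imbalance in a single trial.** With a baseline SD of 2.2, the between-arm difference in mean baseline pain has SD 2.2 × √(2/63) = 0.39 points. The crude risk difference moves by ρ × √(0.4 × 0.6)/s_B per point of imbalance. That is 0.24 × 0.49/2.2 = 5.3 percentage points at ρ = 0.24, and 0.37 × 0.49/2.2 = 8.2 at ρ = 0.37. A one-SD imbalance therefore shifts GROC by about 2 to 3 percentage points. The standard error of the crude risk difference is √(2 × 0.24/63) = 8.7 points, so the shift is about a quarter to a third of it.

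**The case against.** The strongest reply is that nothing here is wrong. Under 1:1 randomisation with no stratification factor, the unadjusted relative risk and risk difference are valid, and no design variable has to enter the model. GROC has no baseline score, so treating it differently from the scored outcomes is not a contradiction. The article names effect measures and never says unadjusted; a fuller plan, not shown, could add covariates. All of this stands, and it limits the point to a suggestion about efficiency. What remains is that the article does fix a method, names covariates in the adjacent sentence, and already collects the variable that would help.

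Two stronger readings are tempting, and the protocol supports neither.
- A reader might infer that uncorrected chance imbalance makes the GROC result biased. It does not: the crude estimate is unbiased over repeated randomisation, and its confidence interval already allows for such imbalance. Adjustment only removes the part of that noise that baseline pain explains.
- A reader might infer a large gain for co-interventions, because the questionnaire at enrolment records "major medical conditions, medications and foot pain duration". Under an assumed risk of 0.80 in baseline users of pain relief against 0.25 in non-users, the variance would fall by about 30%. The protocol gives no basis for those risks. The section on co-interventions counts treatments newly taken up, including advised topical drugs and footwear changes, and participants are asked to try to avoid co-interventions. A drug continued from baseline may not count as new, so even the direction of prediction is uncertain.

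**Conclusion.** The point holds as a minor improvement to one secondary outcome. For dichotomised GROC, the plan passes over a baseline covariate that it already collects. The cost is about 0% to 13% of the variance of the risk difference. The upper end needs equal pain SDs at baseline and week 12 and a strong link between GROC and pain change. If the entry threshold narrows the baseline SD, the gain is about 0% to 6% and may be nil. In the trial that is run, a typical chance imbalance could move the crude risk difference by about 2 to 3 percentage points if the baseline SD is 2.2, and by less if it is smaller. The crude comparison remains valid and unbiased. For co-interventions no gain can be shown from the protocol. The primary analysis, already adjusted for baseline, and N = 140 are unaffected.

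**What to change.** Add to the Statistical analysis section, before any unblinded analysis: dichotomised GROC will be analysed by logistic regression on arm and baseline NRS pain; predicted risks will be averaged over all analysed participants under each arm in turn (marginal standardisation) to give an adjusted risk difference and relative risk with 95% confidence intervals; the number needed to treat will be taken from the adjusted risk difference; crude figures will be reported as a supplement.

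The same adjustment for co-intervention use is optional. Adverse events should stay crude.

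The cost is a few sentences and a short script, with no new data, visits or participants. The downside is one modelling step more than a two-by-two table. Fixing the covariate in advance also avoids a post hoc decision about adjustment if baseline pain turns out to differ between arms.

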**Methods:**

This will be a parallel‐group randomised controlled superiority trial. One‐hundred and forty community‐dwelling people with painful midfoot OA will be randomised to receive either arch contouring foot orthoses or flat sham inserts. Outcome measures will be obtained at baseline, 4, 8 and 12 weeks; the primary endpoint for assessing efficacy being 12 weeks. The primary outcome measure will be average midfoot pain whilst walking over the last 7 days on an 11‐point numerical rating scale. Secondary outcome measures include function (walking/standing subscale of the Manchester–Oxford Foot Questionnaire), participants' perception of overall treatment effect (self‐reported global rating of change on a 15‐point Likert scale), physical activity (Incidental and Planned Exercise Questionnaire), general health‐related quality of life (Short Form‐12 Version® 2.0), use of co‐interventions and adverse events.

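### The two planned missing-data sensitivity analyses, complete case and last observation carried forward, do not show how far missing-at-random must fail before the primary conclusion changes

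*Protocol article*

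**What the plan says.** All of the following is in the protocol article.

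- **Main handling of missing data (section 2.20):** "Multiple imputation will be used to replace any missing data using five iterations, with sex, age, baseline scores and group allocation as predictors".
- **Main model (section 2.20):** for continuous outcomes, "analysis of covariance (ANCOVA) with baseline scores and intervention group entered as independent variables", compared at 12 weeks.
- **Stated purpose of the sensitivity analyses (section 2.20):** "We will assess the robustness of the results from our analyses using the following conditions". Two conditions follow: "only analyse participants who provide outcome data and (ii) last observation carried forward". A further sensitivity analysis is per-protocol; it concerns adherence, not missing data.
- **When the primary outcome is measured:** section 2.12 says "The primary outcome will be measured prior to allocation at baseline and at 12 weeks (the primary endpoint"; the abstract (Methods) says "Outcome measures will be obtained at baseline, 4, 8 and 12 weeks".
- **Expected loss (section 2.19):** 10%, with SD 2.2 points and a target difference of 1.1 points.

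**The concern.** A sensitivity analysis for missing data is useful if it changes the untestable assumption and shows what happens to the answer. The main analysis assumes that, given group, baseline score, sex and age, people without a 12-week score resemble those with one. Complete-case ANCOVA assumes the same given group and baseline, so its agreement with the main result is weak evidence that the assumption is sound.

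Last observation carried forward makes a different assumption, namely no change since the last score, with that score treated as if observed at 12 weeks. This is one point with no scale. If it disagrees with the main result, the reader cannot tell which of the two is wrong.

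The primary outcome is self-reported pain, and section 2.17 plans to count withdrawals due to adverse events. Leaving because the inserts do not help or cause discomfort is therefore plausible, and the article would claim robustness without having graded that possibility.

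**Working it through.** **1. The plan's own figure.** Inputs from section 2.19: difference 1.1, SD 2.2 (d = 0.5), power 80%, alpha 0.05 (two-sided assumed), loss 10%. Normal approximation: n per arm = 2 × (1.96 + 0.84)² / 0.5² ≈ 62.7, so 63; total 126; 126 / 0.90 = 140. The stated 140 reproduces and leaves 63 completers per arm. (The noncentral t gives 64 per arm and 143 in total, a trivial difference.)

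**2. Complete case against multiple imputation.** The check simulated 2,000 trials per scenario with N = 140, SD 2.2 and five imputed data sets from sex, age, baseline and group. Assumptions not in the documents: baseline-to-follow-up correlation 0.5, a mean fall of 1.5 points by week 12 in both arms, sex and age not prognostic, and the dropout models.

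| Scenario (about 10% missing per arm) | Full data | Imputation | Complete case |
|---|---|---|---|
| Completely at random | -1.10 | -1.10 | -1.10 |
| Orthoses-arm dropout depends on unseen week-12 pain | -1.09 | -1.28 | -1.28 |
| Orthoses-arm dropout depends on week-8 pain | -1.11 | -1.22 | -1.22 |

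Mean estimates agreed within about 0.002 points in every scenario, with a mean absolute difference of about 0.04 in single trials. In the last two rows both methods are biased, by about 0.19 and 0.11 points, and still agree.

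**3. Last observation carried forward.** If section 2.12 is right, the last pain score is the baseline score. Under the same assumptions an orthoses dropout is then placed 1.5 + 1.1 = 2.6 points above comparable completers, and a sham dropout 1.5 points above. The shift in the estimate is (orthoses loss × 2.6) − (sham loss × 1.5):

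- 10% / 10%: 0.26 − 0.15 = +0.11, so -1.10 becomes -0.99.
- 15% orthoses / 5% sham: 0.39 − 0.075 = +0.315, so -1.09 becomes about -0.77.
- 5% orthoses / 15% sham: 0.13 − 0.225 = −0.095, so -1.10 becomes about -1.20.

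The simulation gave -0.99, -0.77 and -1.20. If the abstract's schedule is right and week 4 or week 8 is carried forward, it gave -1.06, -0.96 and -1.15. Loss was ignorable in all three cases and imputation was unbiased, so the error belongs to carrying forward, and its sign depends on which arm loses more.

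**4. What a graded analysis would show.** If a shift δ is added to imputed 12-week scores, the effect moves by (orthoses loss × δ in orthoses) − (sham loss × δ in sham). At 10% loss, shifts of 1, 2 and 3 points in the orthoses arm alone take -1.10 to -1.00, -0.90 and -0.80. At an assumed 20% loss they take it to -0.90, -0.70 and -0.50.

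Tipping point at 10% loss = (|effect| − 1.96 × SE) / 0.10, where SE = 2.2 × √(2/63) × √(1 − r²). The baseline correlation r is not in the documents, so a range is shown.

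| r | SE | Observed -0.8 | Observed -1.1 |
|---|---|---|---|
| 0 | 0.392 | (0.8 − 0.768) / 0.10 ≈ 0.3 | (1.1 − 0.768) / 0.10 ≈ 3.3 |
| 0.5 | 0.339 | (0.8 − 0.665) / 0.10 ≈ 1.3 | (1.1 − 0.665) / 0.10 ≈ 4.3 |

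This holds the SE fixed and ignores the limit of the scale at 10, so it is approximate.

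**The case against.** **Complete case need not agree.** A reader might infer that the two analyses are bound to give the same answer. They are not: the imputation model also uses sex and age. In a further simulation, age correlated 0.2 to 0.3 with week-12 pain and age-related dropout ran in opposite directions in the two arms. Complete case minus imputation then averaged -0.05 to -0.16 points. That pattern was chosen to be unfavourable; without arm-dependent dropout the average difference was 0.00. So they usually nearly agree, but need not. Complete case as a supportive analysis is no error.

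**Carrying forward does depart from missing-at-random.** A reader might also infer that neither analysis lets dropouts fare worse than similar completers. On section 2.12's schedule that is wrong: baseline carried forward gives dropouts no improvement, which is worse than completers who improve. In the scenario where dropout followed unseen week-12 pain, it gave -1.09 and so landed on the full-data value, while imputation gave -1.28. This objection stands against the stronger reading. It does not rescue the method as a check. Under ignorable 15% / 5% loss it differed from imputation by even more (-0.77 against -1.09), and there imputation was right. A gap between the two cannot be interpreted by itself.

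**An analysis plan may add more.** It may, and the absence of a tipping-point analysis from an article would be no finding in itself. Section 2.20, however, names the two conditions and says what they are for, so the point is about a stated choice.

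**The effect is small at the planned loss.** This stands, and it limits the weight of the point.

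**Conclusion.** The point holds in limited form. Complete case is nearly redundant with the main analysis as a test of missing-at-random. Last observation carried forward is a real departure from it, but a single ungraded one of uncertain direction, and its meaning depends on which of two conflicting schedules applies. Neither shows how far the assumption must fail before the conclusion changes.

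At 10% loss a clear result near -1.1 would survive any but a large one-arm departure, whereas a borderline result near -0.8 could be overturned by a small one. Higher or unequal loss makes this worse. The tipping values rest on SD 2.2, 63 completers per arm and an assumed baseline correlation of 0 to 0.5. The simulated biases rest on assumed trajectories and dropout models. The near-agreement of complete case and imputation rests mainly on their shared use of baseline and group. The documents do not support a claim that the primary analysis is invalid; this is an inexpensive improvement.

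**What to change.** 1. In section 2.20, replace last observation carried forward with delta-adjusted multiple imputation of the primary outcome. Add a graded range of NRS shifts to the imputed 12-week scores, capped to the 0 to 10 scale, in the orthoses arm only, the sham arm only, and both. Justify the range in advance and report the shift at which the conclusion changes. With equal loss a common shift in both arms largely cancels, so the one-arm versions carry most of the information.
2. Keep complete case, labelled as supportive only.
3. Reconcile the abstract with section 2.12 on whether midfoot pain is scored at weeks 4 and 8. If it is, those scores can also enter the imputation model.
4. Fix these choices before the biostatistician is unblinded.

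Cost: a few lines of code on data sets that are already imputed, with no new data or participants. The drawback is that the stated conclusion may be slightly less firm.
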